### **8.3.1. Intervention arm**

Those randomised to the 'Relaxed' Group will receive K+ supplementation only if their serum [K+] drops below or equals 3.6mEq/L.

### **8.3.2. Control arm**

Patients randomised to the 'Tight' group will receive K+ supplementation if their serum [K+] falls below 4.5 mEq/L (current practice).

### **8.3.3. Blinding**

Blinding patients and clinical staff to the treatment allocation is not possible. The analysis of the outcomes and holter monitor data will be carried out blind to the treatment allocation.

## **8.4. Trial treatment**

The trial treatment will start when participants are admitted to the ICU or another post-operative care facility after their surgery. The participant will undergo regular blood investigations, as per current practice. The frequency of [K+] monitoring will be according to local protocols, clinician/nursing staff preference and clinical need. All other treatments will be given according to standard clinical care and clinician's preference.

The administration route used for all potassium replacement will be prescribed according to clinician preference and given according to existing standardised protocols. This may include intravenous (IV) or oral potassium formulation, administration of potassium-rich nasogastric feeding regimens, recommending the consumption of potassium-rich foods or avoidance of potassium losing drugs.

The use of IV magnesium, beta-blockers and anti-dysrhythmic agents will be as per current practice in both groups.

The trial treatment period will end 120 hours (5 days) after initial admission to ICU/post-operative care facility, discharge from hospital, or with occurrence of a clinically-identified episode of AF (see Section 8.4.1) – whichever occurs first.

### **8.4.1. Patients with AF**

Once a participant has a trial-defined period of AF (see Section 6.2.6.1), there will be no restriction on potassium supplementation and the participant should be treated according to current practice. However, holter monitoring and data collection should continue until the end of the 120 hours or discharge from hospital.

## **8.5. Holter monitoring**

In addition to the usual care, participants will also be asked to wear an external heart rhythm monitor for up to 120 hours (5 days) following their CABG surgery. This will monitor their heart rhythm for any irregular heart rhythms conditions such as AF.

Holter monitor data will be reviewed by a core laboratory group based at Wythenshawe Hospital, Manchester University NHS Foundation Trust. Pseudonymised patient data will be analysed blinded to participant allocation, with some delay to the acute episode of care

and will only be reviewed post-hoc. If the analysis flags up any malignant dysrhythmias, then these will be fed back to the participant's primary care team, as and when that information becomes available. It is important to note that in clinical practice, holter monitor data are diagnostic, but not prognostic, and the way they are used here in the context of a research trial is no different.

### **8.6. Follow-up**

All participants will be followed up 6 months (+/- 1 month) after their surgery. Follow-up will occur either in person, via a telephone call, email or post. An EQ-5D-5L questionnaire will be completed by the patient at this time. Participants will be asked to provide information about further incidences of AF and other heart rhythm problems, and stroke after their hospital discharge, if known.

Participants will also be followed up remotely via NHS Digital for any hospitalisations for AF between discharge and 6 months post-surgery.

### **8.7. End of trial**

The end of the trial is defined as last participant, last follow-up.

## 9. Data collection

### 9.1. Trial treatment period

The trial treatment period commences after surgery when the participant is admitted to ICU or another post-operative care facility after their surgery. The participant's inclusion into the trial and randomised allocation must be clear upon admission to ICU or another post-operative care facility.

**Period 1** (0–24 hours post-admission to ICU)

**Period 2** (24-48 hours post-admission to ICU)

**Period 3** (48-72 hours post-admission to ICU)

**Period 4** (72-96 hours post-admission to ICU)

**Period 5** (96-120 hours post-admission to ICU)

**Follow-up** (6 months (+/- 1 month) post-CABG surgery)

### 9.2. Trial Procedures Table

|                                | Before Surgery | Day of Surgery | ICU Stay
(commences on admission to ICU) |          |          |          |          | Discharge | Follow-up |
|--------------------------------|----------------|----------------|---------------------------------------------|----------|----------|----------|----------|-----------|-----------|
|                                |                |                | Period 1                                    | Period 2 | Period 3 | Period 4 | Period 5 |           |           |
| Review of eligibility criteria | X              |                |                                             |          |          |          |          |           |           |
| Consent                        | X              |                |                                             |          |          |          |          |           |           |
| Baseline                       | X              |                |                                             |          |          |          |          |           |           |
| Randomisation                  |                | X              |                                             |          |          |          |          |           |           |
| Trial treatment                |                |                | X                                           | X        | X        | X        | X        |           |           |
| Holter Monitoring              |                |                | X                                           | X        | X        | X        | X        |           |           |
| Clinical events                |                |                | X                                           | X        | X        | X        | X        | X         | X         |
| Safety monitoring              |                |                | X                                           | X        | X        | X        | X        | X         | X         |
| EQ-5D-5L                       | X              |                |                                             |          |          |          |          |           | X         |

### 9.3. Data collection

Data collected for all participants will include measurements of daily serum electrolytes / renal function and collation of adverse events attributed to K+ replacement, including gastrointestinal symptoms from oral K+ replacement. Medication at hospital discharge will be collated, including whether anticoagulation is commenced for atrial fibrillation. Additional staff time for delivering the intervention will be recorded on site visits and will be informed by expert clinical view.

Detailed information will be collected on the resource use associated with delivering each protocol, including the total number of replacement K+ interventions and the number of tests for monitoring potassium levels.

The perceived clinical impact (symptomatic/asymptomatic) of a dysrhythmia will be noted by the clinical staff. Participants in either group who experience AF (as defined in Section 6.2.6.1) will be deemed to have met the primary end point.

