### **9.4.3. Period 1-5**

- Potassium blood readings (measured as per clinician preference and local pathways)
- Potassium administration (dose and route)
- Clinically significant pacing modes
- Restenotomy
- Clinical events
- Safety monitoring

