## 11. Safety monitoring

### 11.1. Definition

**Unexpected** events that have not been defined as outcomes (see Section 6.2.1, 6.2.2), expected complications of potassium supplementation, expected complications of CABG surgery or expected complications of usual clinical care (see Section 11.2) should be reported as either a serious adverse event (SAE) or non-serious adverse event (NSAE), depending on their severity. Safety reporting for each patient should commence from time of randomisation to completion of follow-up at 6 months after the CABG surgery.

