### 11.2. Expected adverse events

- Skin irritation from ECG electrodes
- Hyperkalaemia ( $[K^+] \geq 5.5$  mEq/L)
- Line site complications (phlebitis, infection etc.)
- Nausea
- Constipation, vomiting (due to receiving oral potassium supplementation)
- Myocardial infarction
- Stroke
- Renal failure requiring dialysis
- Renal impairment not requiring dialysis
- Wound infection (sternum or donor site)
- Return to theatre for bleeding
- Prolonged mechanical support
- Post-op delirium
- Non-cardiac chest pain
- Heart failure
- Pleural effusion
- Chest drain insertion
- Pericardial effusion
- Chest infection (pneumonia)
- Lung atelectasis
- Pneumothorax
- Shortness of breath caused by any of the above

- Blood transfusion
- Pericarditis
- Ulnar nerve paraesthesia
- Heart block requiring pacemaker
- Urinary tract infection
- Suprapubic catheter
- Urinary retention
- Intra-aortic balloon pump insertion

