### **11.5. Reporting unexpected adverse events**

Investigators will make their reports of all unexpected adverse events, whether serious or not, to the CTU at LSHTM.

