#### **11.5.2. Assessment of causality**

Probable: A causal relationship is clinically / biologically highly plausible and there is a plausible time sequence between onset of the adverse event and the RIC procedure.

Possible: A causal relationship is clinically / biologically plausible and there is a plausible time sequence between onset of the adverse event and the RIC procedure.

Unlikely: A causal relationship is improbable and another documented cause of the adverse event is most plausible.

Unrelated: A causal relationship can definitely be excluded and another documented cause of the adverse event is most plausible.

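### Gastrointestinal side effects of potassium are collected only when unblinded staff attribute them to potassium, so any between-arm count of them leans against the tight arm

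*Protocol*

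**What the plan says.** - **What is collected.** Among the data for all participants, Protocol 9.3 lists the "collation of adverse events attributed to" potassium replacement, and names gastrointestinal symptoms arising from oral replacement as an example.
- **Who judges.** Section 8.3.3 states: "Blinding patients and clinical staff to the treatment allocation is not possible". Only the analysis of outcomes and of Holter data is blind.
- **What is exempt from reporting.** Section 11.1 asks for unexpected events to be reported as serious or non-serious adverse events. It sets aside trial outcomes and "expected complications of potassium supplementation, expected complications of CABG surgery or expected complications of usual clinical care", and points to 11.2 for the list. That list includes nausea without qualification, "Hyperkalaemia" with a laboratory threshold, line-site complications, and "Constipation, vomiting (due to receiving oral potassium supplementation").
- **What is reported whatever its cause.** Section 11.5 says: "Investigators will make their reports of all unexpected adverse events, whether serious or not, to the CTU at LSHTM". The causality scale in 11.5.2 runs down to "Unrelated: A causal relationship can definitely be excluded", so causality is graded after reporting and is not a condition for it.
- **What is measured in both arms without attribution.** Section 9.4.3 collects "Potassium blood readings (measured as per clinician preference and local pathways"). Section 9.4.4 adds central line duration. Section 6.2.2 lists non-AF dysrhythmias, mortality and lengths of stay.

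**The concern.** Section 4.1 describes oral potassium as badly tolerated, with marked nausea and gastrointestinal effects, and 4.3 calls the routine practice unpleasant and possibly hazardous. If the relaxed target proves non-inferior for AF, better tolerability will be part of the argument for adopting it.

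Randomisation could give a fair answer on tolerability, but only if symptoms are recorded in the same way in both arms. Under 9.3 a symptom enters the data by being attributed to potassium. A relaxed-arm patient who vomits but has had no potassium has nothing to attribute it to, whereas a tight-arm patient with the same symptom usually does. The people making the judgement know the arm and may hold the same view of potassium as the protocol. Symptoms that were never written down cannot be recovered by any later analysis.

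**Working it through.** **1. How each symptom is captured**

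| Symptom | Patient given oral potassium | Patient given none |
|---|---|---|
| Nausea | Collated under 9.3 if attributed; exempt from 11.3–11.5 because listed in 11.2 | No attribution possible under 9.3; still exempt because the 11.2 entry is unqualified |
| Constipation, vomiting | Collated under 9.3 if attributed; exempt when due to oral potassium | Not covered by the qualified 11.2 entry, so either an unexpected event or a complication of surgery or usual care under 11.1 |

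For nausea, the only explicit route is attribution. For constipation and vomiting, the same symptom can follow different routes according to whether potassium was given, so the counts from those routes are not comparable. Attribution itself is not defined for this trial: two grades in 11.5.2 refer to an RIC procedure, a term that is absent from the glossary and is not potassium.

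**2. Inputs**

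- Feasibility study, section 4.2: potassium needed by 80/81 = 98.8% of the tight arm and 19/79 = 24.1% of the relaxed arm. Both percentages reproduce.
- Arm size for illustration, section 12.1: (1.960 + 1.282)² × (0.65×0.35 + 0.63×0.37) / (0.10 − 0.02)² = 10.51 × 0.4606 / 0.0064, which rounds up to 757 per arm, or 1514 in all, as stated. With 10% loss, 757/0.9 rounds up to 842 per arm, or 1684, as stated.
- Assumed, not in the protocol: a background symptom rate *b*, equal in both arms (no true effect), and a chance *a* that staff attribute a symptom to potassium in a patient who was given it.

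**3. Recorded rates under no true effect**

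Recorded rate = *b* × *a* × share given potassium. In the ratio of tight to relaxed, *b* and *a* cancel:

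- feasibility shares: 98.8 / 24.1 = 4.1;
- half of relaxed patients given a dose: 98.8 / 50 = 2.0.

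The second case is plausible for two reasons. Section 4.1 gives a median of one dose in the relaxed arm, which would mean that at least half received one, although the same sentence says that most received none. Section 8.4.1 also lifts the restriction once AF occurs. If 35% of the remaining relaxed patients (the tight-arm AF rate in 12.1, borrowed as an assumption) then received potassium, exposure would be 0.241 + 0.759 × 0.35 = 0.51, and the ratio about 1.9.

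The spurious difference is *b* × *a* × 74.7 points with the feasibility shares, or *b* × *a* × 48.8 points with half exposed:

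| *b*, *a* | Difference at 24.1% exposed | Difference at 50% exposed | Chance of nominal significance (24.1% / 50%) |
|---|---|---|---|
| 10%, 10% | 0.75 points | 0.5 points | 46% / 20% |
| 30%, 30% | 6.7 points | 4.4 points | >99% / 93% |
| 50%, 50% | 18.7 points | 12.2 points | >99% / >99% |

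The last column is for 757 per arm at two-sided 5%, as Φ(difference/SE − 1.96) with SE = √[(p₁(1−p₁) + p₂(1−p₂))/757]. For the first row at 24.1%: rates 0.99% and 0.24%, SE 0.40 points, Φ(1.86 − 1.96) = 0.46. With symptoms recorded regardless of attribution, the expected difference in this model is zero.

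**The case against.** The strongest reply is that 11.2 is a list of exemptions, not a rule for what to record, and that most harm data do not depend on attribution. Much of this stands, and it rules out four stronger readings that a reader might infer.

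- **That all treatment harms are recorded only if attributed.** The list in 9.3 is not worded as exclusive, unexpected events are reported whatever their cause, and the laboratory, line, rhythm and mortality data need no attribution.
- **That a patient given no potassium cannot have vomiting or constipation recorded.** Because the 11.2 entry is tied to oral potassium, the same symptom without it may count as unexpected and be reportable.
- **That leaving low potassium off the 11.2 list, while high potassium is on it, favours the relaxed arm.** Listing removes an event from reporting. An unlisted low-potassium event could be reportable, which leans the other way, and both extremes can be derived from the readings.
- **That the distortion is a firm fourfold.** The feasibility shares count patients with a measurement below the threshold, not patients given oral potassium, and 8.4 allows intravenous, dietary and other routes. The feasibility count used values below 3.6 mEq/L, while 8.3.1 also includes 3.6 itself.

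It is also fair that no adverse-event endpoint appears in 6.2.2 or 12.3.2, and that the eCRF pages behind the clinical-event and safety-monitoring rows in 9.2 are not shown and may hold symptom tick boxes. But those rows name no symptoms, and the one rule that does name gastrointestinal symptoms depends on attribution. Collating attributed events is a legitimate description of treatment burden. It does not support a comparison between arms.

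**Conclusion.** The point holds for one group of harms: the expected, subjective gastrointestinal side effects of potassium. As written, the protocol yields a count of these that depends on exposure and on unblinded judgement, and that count leans against the tight arm when there is no true difference. The direction follows from the rule. The size does not: a ratio of about 2 to 4 rests on the assumed relaxed-arm exposure, on an equal attribution rate in both arms, and on need for any potassium standing in for oral dosing, which the protocol does not give. The absolute differences also depend on assumed symptom and attribution rates.

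The primary non-inferiority result and the sample size are untouched. What is at risk is the descriptive tolerability evidence. The change is worth making because it concerns a stated collection rule and must be made before the data are gathered.

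**What to change.** - **Sections 9.3 and 9.4.3, and the eCRF:** for every participant and each 24-hour period, record nausea, vomiting and constipation as present or absent, whether or not potassium was given and whatever the suspected cause. Keep attribution to potassium as a separate descriptive field.
- **Summary:** present these symptoms by randomised arm. Derive high and low potassium from the readings already collected.
- **Sections 11.1 and 11.2:** make the entries consistent, so that the same symptom follows the same reporting route in both arms. Remove the causal qualifier on constipation and vomiting only once the symptom record is in place; removing it alone would widen the exemption and lose reports.

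The cost is a few extra eCRF fields per period and the staff time to complete them. No treatment changes. Some reporting bias will remain, because patients and staff still know the allocation, but capture will no longer depend on having received potassium.

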## **9.4. Trial procedures**

### **9.4.1. Before surgery**

- Consent
- Quality of life questionnaire (EQ-5D-5L)

### **9.4.2. Baseline**

- Age
- Gender
- Ethnic origin
- Cardiac medication and indication (including beta-blockers, calcium channel blockers, ACE-inhibitors, all blockers, aldosterone antagonists, anticoagulation)
- Medical history: family history of dysrhythmia (and details), chronic obstructive pulmonary disease/lung disease, diabetes mellitus (and type), hypertension, myocardial infarction, chronic kidney disease, transient ischaemic attack or stroke / cerebrovascular accident
- Imaging data: Left ventricular ejection fraction / left atrial size, mitral regurgitation or stenosis (defined as moderate or worse) and estimated pulmonary artery systolic pressure
- HAS-BLED and CHADSVASC scores will be calculated

### **9.4.3. Period 1-5**

- Potassium blood readings (measured as per clinician preference and local pathways)
- Potassium administration (dose and route)
- Clinically significant pacing modes
- Restenotomy
- Clinical events
- Safety monitoring

### **9.4.4. Discharge (from ICU and hospital)**

- ICU length of stay
- Hospital length of stay
- Medications
- Duration of central venous lines left in situ
- Clinical events
- Safety monitoring

#### **9.4.5. Follow-up**

- Quality of life questionnaire (EQ-5D-5L)
- Clinical events
- Safety monitoring

### **9.5. Compliance and loss to follow-up**

#### **9.5.1. Loss to follow-up**

The majority of participants remain in hospital for 5 days after their CABG surgery, so loss to follow up over that period is unlikely.

The participants will subsequently be followed up at 6 months following CABG surgery. Participants will be given an ID card to remind them they are taking part in the study and to optimise event reporting during follow-up to the trial team.

#### **9.5.2. Compliance**

Given that a large number of different health providers care for post-operative patients in different hospital locations, it is conceivable that protocol violations will occur. These violations may either result from a patient from the 'Relaxed' group being treated as if they are in the 'Tight' Group, or visa-versa.

It is more likely that protocol violations will occur once the patient leaves the ICU and arrives on the post-operative step down ward. These wards have lower staff-to-patient ratios and a higher turnover of staff members. It is critical for the success of the trial that junior doctors and nursing staff in all the post-operative areas where patients may spend time are informed about the trial's goals and protocols. Patients, as they are not blinded, can also play a role in reminding staff which group they have been allocated to. The trial is not blinded to caregivers on the ICU/surgical ward so there is always a risk of concomitant treatment bias, but training will be put in place to minimise this.

### **9.6. Data Handling and Record Keeping**

Data will be entered onto an online database and stored securely on Rackspace servers; <http://www.rackspace.co.uk> and managed by Sealed EnvelopeTM. Data will be kept for 20 years following completion of the trial.

Pseudonymised patient data will be stored on non-networked PCs at the Core Lab at Wythenshawe Hospital, Manchester University NHS Foundation Trust, with regular external code-locked USBs (with or without secure cloud back-up).

The data controller for the trial is the Chief Investigator (Barts Health NHS Trust are the data controller's organisation) and the data processor is LSHTM and Wythenshawe Hospital.

Patient data will be kept confidential and managed in accordance with the Data Protection Act (2018), NHS Caldecott principles, the Research Governance Framework for Health and Social Care, and the conditions of Research Ethics Committee Approval.

## 10. Monitoring and Audits

The conduct of the trial will be supervised by trained staff from the LSHTM CTU. The trial will be monitored on a regular basis using central statistical monitoring. Full details will be available in the monitoring standard operating procedure (SOP) and the trial will be monitored according to this agreed plan.

Local investigators shall ensure that all trial data are available for trial-related monitoring, and sponsor and regulatory authority audits. Sponsor also holds the right to monitor or audit the study.

